## Methods/design

### Study design

This is a single-center (UCLA), single-arm, prospective phase II study with a safety lead-in. 43 subjects are planned. Each subject will receive the same PULSAR radiation therapy course as described below. The first 15 enrolled patients will be evaluated in the safety lead-in portion. If 5 or more of these 15 patients experience CTCAE v5.0 grade 3 or 4 or any patient experiences a grade 5 toxicity probably attributable to PULSAR during or within three months after completion of PULSAR, the study will be stopped for safety concerns; otherwise, the study will proceed, and those initial 15 patients will be included in the 43 subject sample. The trial schema is shown in Fig. 1.

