#### AE relationship to the study intervention

The relationship of an AE to the study intervention should be assessed by an investigator using the following guidelines in Table 2. The causality assessment must be made based on the available information and can be updated as new information becomes available.

**Table 2 Tab2:** AE relationship to study intervention

Relationship to intervention	Comment
Definitely	Previously known toxicity of the intervention; or an event that follows a reasonable temporal sequence from administration of the intervention; that follows a known or expected response pattern to the suspected intervention; that is confirmed by stopping or reducing the dosage of the intervention; and that is not explained by any other reasonable hypothesis
Probably	An event that follows a reasonable temporal sequence from administration of the intervention; that follows a known or expected response pattern to the suspected intervention; that is confirmed by stopping or reducing the dosage of the intervention; and that is unlikely to be explained by the known characteristics of the subject’s clinical state or by other interventions
Possibly	An event that follows a reasonable temporal sequence from administration of the intervention; that follows a known or expected response pattern to that suspected intervention; but that could readily have been produced by a number of other factors
Not Related/ Unlikely Related	An event that can be determined with certainty to have no relationship to the study intervention

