##### Secondary endpoints

Measurement of grade 3 or higher treatment-related toxicity during or within 24 months after completion of PULSAR, according to the CTCAE v5.0.Disease progression free survival (PFS), defined as the time from enrollment to the first objectively documented disease progression, either in or out of the treated field per radiographic and/or clinical evaluation, or death due to any cause. Participants who experience death or are lost to follow-up prior to 1 year will be assessed by their last radiographic/clinical evaluation.Overall survival (OS), defined as the time between enrollment and death of any cause. Participants who are lost to follow-up prior to 1 year will be censored at the date of their last documentation in the medical record system.Impact of PULSAR on symptoms/quality of life as measured by the UW-QoL and FACT-H&N validated questionnaires.Measurement of the frequency of re-simulation and/or adaptive planning required with PULSAR.Evaluation of the standard of care tumor and OAR dosimetry with PULSAR.Evaluation of the safety and efficacy of combination PULSAR and cancer-directed systemic therapy in enrolled patients receiving cancer-directed systemic therapy will be descriptive and exploratory.

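### Read literally, Table 2 lets no death and no event starting after the last fraction be rated Probably related, yet the safety stop rule turns on that word up to three months after treatment

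*Protocol article*

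**What the plan says.** Table 2, under AE relationship to the study intervention, defines Probably by four conditions separated by semicolons and closed with an *and*. The last two begin "that is confirmed by stopping or reducing the dosage of the intervention; and that is unlikely to be explained by the known characteristics". The withdrawal condition is therefore cumulative with the others.

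The neighbouring rows read differently:

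- Definitely opens with an alternative: "Previously known toxicity of the intervention; or an event that follows a reasonable temporal sequence". The first limb has no withdrawal condition; the second limb has one.
- Possibly has no withdrawal condition, but the event must be one "but that could readily have been produced by a number of other factors".
- Not Related/Unlikely Related requires certainty that there is no relationship.

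The stop rule appears in the Abstract, in Study design and in Safety lead-in/interim analysis. The trial stops when either of two triggers is met. One is grade 3-4 toxicity in at least 5 of the first 15 patients. Study design words the other as follows: "any patient experiences a grade 5 toxicity probably attributable to PULSAR during or within three months after completion of PULSAR". Under PULSAR treatment the course is five fractions, 14 days apart with a tolerance of 10 days either way. Adaptive radiation planning extends the upper tolerance to 21 days after re-simulation and re-planning.

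**The concern.** Confirmation by stopping or reducing the dose is a test made for a drug that can be withheld. It can be applied between fractions, when a later fraction can be held or the course ended. Once the last fraction has been given, nothing is left to stop or reduce, and a fatal event cannot be tested in this way at any time.

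The stop rule uses the same word, probably, and deliberately looks beyond the end of treatment. If an investigator applies Table 2 as written, the rule's key category cannot hold a death, or an event that begins in the follow-up part of its own window. This is a conflict between two current parts of the article, not a detail left to another document. It bears on the only numerical safety stopping rule the article states, for a technique that the Background says has not been comprehensively studied and has no listed trial in head and neck cancer.

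**Working it through.** **Step 1. Where can a post-treatment event or a death be placed?** Take an event that starts after the last fraction, or a death, with no plausible alternative cause.

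| Table 2 row | Can it hold the event, read literally? |
|---|---|
| Definitely, first limb | Yes, if it is a previously known toxicity |
| Definitely, second limb | No, withdrawal confirmation required |
| Probably | No, withdrawal confirmation required |
| Possibly | No, other factors must readily explain it |
| Not Related/Unlikely Related | No, absence of a relationship must be certain |

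A known toxicity has one route, and the stop rule does not say whether that category counts. An event that is not a known toxicity has no row.

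**Step 2. Which triggers are affected?** The grade 5 trigger carries the attribution words in every statement of the rule. For grade 3-4 the text is unclear. In Study design, the word toxicity and its attribution appear once, after grade 5, and can be read as covering grades 3 and 4 too. In Safety lead-in/interim analysis, the grade 3-4 trigger is a complete clause without attribution, and the attribution words follow only in the separate grade 5 clause.

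**Step 3. How much of the window is affected?** There are four intervals between five fractions, and three months is taken as about 91 days. The share of the window after the first fraction that lies after the last fraction is 91 / (91 + 4 × interval).

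- 14 days (nominal): 91 / (91 + 56) = 91/147 = 62%
- 4 days (14 − 10): 91/107 = 85%
- 24 days (14 + 10): 91/187 = 49%
- 35 days (14 + 21, re-planning before every later fraction): 91/231 = 39%

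These are shares of calendar time, not of events.

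**Step 4. What could it do to the stop rule?** The article states no operating characteristics, so there is no figure to reproduce. Let *p* be the true per-patient rate of qualifying toxicity and *f* the share that can be counted. Both are assumptions. For grade 3-4, and only if attribution applies to it, P(stop) = P(X ≥ 5) with X ~ Binomial(15, p × f):

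| p | f = 1 | f = 0.75 | f = 0.5 |
|---|---|---|---|
| 20% | 16.4% | 6.2% | 1.3% |
| 30% | 48.5% | 23.4% | 6.2% |
| 40% | 78.3% | 48.5% | 16.4% |

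For grade 5, P(at least one in 15) = 1 − (1 − p × f)^15. At an assumed rate of 5% this is 53.7% with f = 1, 31.6% with f = 0.5 and 0% with f = 0. With f = 1 it is 14.0% at a rate of 1% and 79.4% at 10%.

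**The case against.** Several points limit how far this reaches.

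- **Known toxicities have a route.** Typical radiation injury can be rated Definitely under the first limb. The Background reports institutional experience with HyperArc SBRT at 55 Gy in five fractions, so the set of known toxicities is not empty. This stands: a claim that the rule cannot count post-treatment events at all goes too far.
- **Probably attributable is naturally read as at least probable.** A rule that counted probable and ignored definite toxicity would make no sense. This is a fair reading, but the article does not state it. It also does not help an event that fits neither row.
- **Table 2 is guidance.** Causality "should be assessed by an investigator using the following guidelines in Table 2", and "The causality assessment must be made based on the available information and can be updated as new information becomes available". A sensible investigator may pass over the withdrawal condition. That softens the effect in practice, but the rule then works only when a written criterion is ignored.
- **Other safeguards exist.** AE and SAE reporting sends every SAE to the DSMB whatever its relationship to treatment, with deaths reported within 2 business days, and the DSMB reviews each SAE monthly. A reader might infer that the lead-in would let a toxic regimen through. The article does not support that.
- **The 24-month toxicity endpoint sets no such threshold.** The endpoint is "Measurement of grade 3 or higher treatment-related toxicity during or within 24 months after completion of PULSAR". Treatment-related is not tied there to Probably or above, and Possibly has no withdrawal condition. A reader might infer that this endpoint will be understated; that does not follow.
- **Large falls in stopping probability are built on assumptions.** With a 40% grade 3-4 rate, 60% of events after the last fraction and none of those countable, the rate counted is 0.40 × 0.40 = 16% and the chance of stopping falls from 78% to 8%. The arithmetic is right. But the rate and the timing are assumed, the Definitely route is ignored, and attribution is taken to apply to grade 3-4.

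**Conclusion.** The point holds in limited form. The Probably row and the stop rule do not fit together, and the rule misfires if both are followed as written. The gap is firm in two places: the grade 5 trigger, and post-treatment events that are not already known toxicities. For known toxicities it depends on whether Definitely counts. For the grade 3-4 trigger it depends on whether the attribution words cover those grades.

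The size that the article itself supports is the share of the window: about 62% at nominal spacing and about 39% to 85% over the permitted intervals, taking three months as 91 days. The stopping probabilities show only the direction and possible scale of the effect, because the article gives neither event rates nor onset times. The conflict should be reconciled before the lead-in is judged.

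**What to change.** 1. In Table 2, delete the withdrawal condition from Probably and from the second limb of Definitely, or apply it only where withdrawal is possible.
2. In the Abstract, Study design and Safety lead-in/interim analysis, state that the stop rule counts events rated Probably or Definitely.
3. In the same three places, state consistently whether attribution applies to grade 3-4 as well as to grade 5.
4. Align the category names. AE evaluation lists five levels starting at related, while Table 2 has four rows starting at Definitely.

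The defect itself needs no new causality criteria and no tightening of the known-toxicity limb. The cost is a wording change to one table, one clause of the stop rule and one list. The downside is that slightly more events may count, so the reported toxicity may look less favourable.

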#### AE action taken regarding study intervention

Where necessary the intervention name will be included in the source documenting the event.

None required: No change in study intervention.Intervention not administered: The study intervention was held.Dose reduced: The study intervention was modified.Dose delayed/interrupted: The study intervention was temporarily stopped.Intervention discontinued: The study intervention was permanently stopped.

#### Treatment of the AE

None: No treatment was required.Medication required: Prescription and/or over-the-counter medication was required to treat the AE.Procedure/Surgery: Medical procedure was required to treat the AE.Other: to be specified in the source documents.

#### AE outcome

Resolved: The participant fully recovered from the AE with no residual effect observed.Resolved with Sequelae: The residual effects of the AE are still present and observable. Include sequelae/residual effects.Persists: The AE itself is still present and observable.Death: Death should be used when death is a direct outcome of the AE.Unknown: Information unavailable

#### Serious Adverse Event (SAE)

An SAE is any untoward medical occurrence that at any dose:

Results in death,Is life-threatening, that is, places the participant at immediate risk of death from the event as it occurred. This definition does not include a reaction that, had it occurred in a more severe form, might have caused death;Requires inpatient hospitalization or prolongation of existing hospitalization, unless hospitalization is for:◦Routine treatment or monitoring of the studied indication, not associated with any deterioration in condition;◦Elective or pre-planned treatment for a pre-existing condition that is unrelated to the indication under study and has not worsened since signing the informed consent;◦Social reasons and respite care in the absence of any deterioration in the participant’s general condition;Results in persistent or significant disability/incapacity;Is a congenital anomaly/birth defect; orIs an important medical event.

Medical and scientific judgment should be exercised in deciding whether expedited reporting is appropriate in other situations, such as important medical events that may not be immediately life-threatening or result in death or hospitalization but may jeopardize the participant or may require intervention to prevent one of the other outcomes listed in the definition above. Examples include allergic bronchospasm, convulsions, and blood dyscrasias or development of drug dependency or drug abuse.

Note:Procedures are not AEs or SAEs, but the reason for the procedure may be an AE or SAE.Pre-planned (prior to signing the informed consent form [ICF]) procedures or treatments requiring hospitalizations for pre-existing conditions that do not worsen in severity are not SAEs.

For events that are serious due to hospitalization, the reason for hospitalization must be reported as the SAE (diagnosis or symptom requiring hospitalization). For deaths, the underlying or immediate cause of death should always be reported as an SAE. Any serious, untoward event that may occur subsequent to the reporting period that the investigator assesses as related to study intervention should also be reported and managed as an SAE. Unlike routine safety assessments, SAEs are monitored continuously and have special reporting requirements. All serious or intervention-related AEs ongoing at the end of treatment visit will be followed until resolution or until the condition is considered chronic/stable by the investigator.

#### AE and SAE reporting

All AEs and SAEs that occur between study enrollment and 6 months after completion of the intervention, will be reported in the eCRF and all SAEs will be reported in the Clinical Research Management System (CRMS) (OnCore). After 6 months after completion of the intervention, only AEs and SAEs suspected to be related to the intervention will be reported.

All events (serious and non-serious) must be reported with investigator’s assessment of the event’s seriousness, severity, and causality to the study intervention. A detailed narrative summarizing the course of the event, including its evaluation, treatment, and outcome should be provided. Specific or estimated dates of event onset, treatment, and resolution should be included when available. Medical history, concomitant medications, and laboratory data that are relevant to the event should also be summarized in the narrative. For fatal events, the narrative should state whether an autopsy was or will be performed, and include the results if available. Source documents (including medical reports) will be retained at the study site and should not be submitted to the Sponsor for SAE reporting purposes.

Disease progression/worsening of disease will not be recorded as an AE on the Adverse Event eCRF. However, events associated with disease progression may be recorded as AEs. Death due to disease progression should be recorded on the Death eCRF.

The study teams must report all SAEs to the JCCC DSMB in a timely manner. Regardless of relationship and expectedness of the event to the study intervention, the PI or their delegate must report the SAE within 10 business days of awareness. In the event of a participant death, the PI or their delegate must report the event within 2 business days of awareness. The SAE submission must note the date of awareness in the event narrative.

To report the SAEs to the JCCC DSMB, the study team enters the SAE information into OnCore, the CRMS. The CRMS generates and sends notifications regarding the submission to the JCCC DSMB administrative team and the study team. Study teams without access to OnCore, may complete the SAE submission form manually and submit it to the JCCC DSMB administrative staff, who will enter the SAE into OnCore on their behalf. The CRMS generates reports for full JCCC DSMB review.

The PI is also responsible for reporting any serious adverse event (SAE) to the sponsor, and any appropriate agency, according to the agency requirements. These include, but are not limited to: UCLA IRB; FDA; and NCI, if it is an NCI sponsored trial.

The collection period for all SAEs will begin after informed consent is obtained and end after procedures for the final study visit have been completed. Any SAEs experienced after this period should only be reported to the Sponsor if the investigator suspects a causal relationship to the study intervention.

In accordance with the standard operating procedures and policies of the local Institutional Review Board (IRB)/Independent Ethics Committee (IEC), the site investigator will report SAEs to the IRB/IEC when applicable.

#### DSMB review of AEs and SAEs

The JCCC DSMB reviews all AEs as part of the summary report review performed quarterly, semi-annually or annually based on the risk level assigned to the study and in accordance with the JCCC Data and Safety Monitoring Plan. The DSMB reviews each SAE monthly and determines if the event(s) warrants modifications to the protocol to ensure subject safety. In their review, the DMSB considers prior occurrences of similar toxicity with the intervention under study, as well as the severity of the event and the likelihood of relation to the study intervention or investigational product. The DSMB may recommend no changes to the study if the event is expected or related to other causes such as underlying disease. To assist discussions and decisions, the DSMB may request the expert advice of another clinical researcher with national experience.

### Data safety, collection, retention, and monitoring

#### Monitoring

The JCCC Office of Regulatory Compliance (ORC) will perform monitoring and auditing activities in accordance with the JCCC Data and Safety Monitoring Plan (DSMP).

#### Data safety monitoring

The JCCC DSMB will serve as the DSMB to review data relating to safety and efficacy, to conduct and review interim analyses, and to ensure the continued scientific validity and merit of the study, according to the JCCC DSMP. There will be quarterly, semi-annually or annual interim review(s) conducted by the DSMB based on the risk level assigned to the study for the purpose of monitoring study conduct and assessing participant safety. Risk level 1 studies are the highest risk and are reviewed quarterly; Risk Level 2 studies are intermediate risk and are reviewed semi-annually; Risk Level 3 studies are the lowest risk and are reviewed annually. Further details regarding the timing and content of the interim reviews via summary reports are included in the JCCC DSMP.

#### Data management

The radiation oncology research staff will be responsible for the database records of study patients. The data will be kept on the research staff computer, under password protection, with the patient information de-identified (study patients will be referred by their coded study number). A chart with all the relevant research patient information will be maintained for each patient by the research coordinator and will be filed in a locked cabinet. Only the research team (study staff, investigators, and project supporting staff) will have the password and key to the data from the study patients.

#### Confidentiality

Study data will be maintained in password protected computer files. Only research personnel will have access to this information. All identifiers will be removed. The patient’s name or other public identifiers will not be included in any information shared with other investigators. The master key that will identify specific study patients to their coded study number will be kept in a separate password protected file on the research staff computer. Only the study staff and the principal investigator will know the password to this file.

### Statistical methods and considerations

#### General

All analyses will be descriptive and will be presented by treatment period and overall as appropriate. Data collected in this study will be presented using summary tables and patient data listings. Continuous variables will be summarized using descriptive statistics, specifically the mean, median, standard deviation, minimum, and maximum. Categorical variables will be summarized by frequencies and percentages.

#### Safety lead-in/interim analysis

The study includes a safety lead-in portion, with formal evaluation on enrollment of the 15^th^ subject. The trial will be stopped if 5 or more patients in the safety lead-in portion experience a serious adverse event, defined as a CTCAE v5.0 grade 3 or 4 toxicity, or if any patient experiences a grade 5 toxicity probably attributable to the intervention during or within three months after completion of PULSAR.

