**Methods:**

This single-arm phase II study will prospectively evaluate PULSAR with HyperArc© software for palliative treatment of head and neck cancer. Patients with de novo or recurrent, localized or metastatic, head and neck cancer who are ineligible for or decline standard of care definitive treatments are eligible for enrollment. Forty-three patients will receive an 11 Gray fraction of radiation every two weeks for a total of five fractions and dose of 55 Gy. Adaptive radiotherapy planning is permitted. A safety and feasibility evaluation will be performed after enrollment of the first fifteen patients whereby the trial will be closed if five or more patients experience a CTCAEv5.0 grade 3 or 4 or any patient experiences a grade 5 toxicity probably attributable to PULSAR during or within three months after its completion. The primary endpoint is one-year local head and neck tumor control. Secondary endpoints include safety, disease progression-free and overall survival, symptomatic impact, frequency of re-simulation and/or adaptive planning, and radiation dosimetry of PULSAR. Additionally, enrolled patients are permitted to receive cancer-directed systemic therapy, including immunotherapy, during PULSAR which may allow for the analysis of the safety and efficacy of this combination.

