#### PULSAR treatment

Daily cone-beam CT will be obtained prior to radiation delivery to verify anatomic location and stability. Treatment will consist of 6, 10, or 15 MV photons directed at the PTV using HyperArc©’s automated non-coplanar VMAT technique. Patients will receive a total of 55 Gray in 5 fractions (biological effective dose with alpha/beta of 10: 115.5 Gray) to the PTV. Patients will receive each 11 Gray fraction of radiation every 14 +/−10 days. Treatment will be terminated early in cases of intolerable treatment-related toxicity, altered clinical context, or the patient declines further treatment.

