**Fig. 2 Fig2:**
[figure not shown]
Trial Calendar. ^1^In primary diagnosis cases, pathologic confirmation is required. In recurrent and/or metastatic diagnosis cases, pathologic confirmation is not required if not beneficial to the patient as standard of care, and diagnosis can be assumed based on clinical and/or radiographic evidence. If available, Human Papillomavirus and/or p16 status will be collected and reviewed. ^2^Within 60 days of CT simulation. ^3^Questionnaires may be administered by telephone or electronically. ^4^May be repeated in between PULSAR fractions per treating physician’s discretion, as per section 6.5. ^5^During PULSAR course, toxicity assessments will occur within 7 days of each radiation fraction and may occur via telemedicine. ^6^May occur via telemedicine. ^7^For patients who undergo re-simulation and re-planning, an extended window of 14 +21/-10 days from most recent radiation therapy fraction to receive the next radiation therapy fraction to accommodate re-simulation scheduling and re-planning time. ^8^This will be the last follow-up for the safety lead-in portion, estimated to be at 12 months after trial opening. If proceeding to the phase II portion, the 15 patients in the safety lead-in portion will continue follow-up as per the study calendar, and all subsequently enrolled patients will follow the study calendar timeline and procedures. †Upon confirmation of eligibility and enrollment in the study, the following will be obtained prior to treatment (if not already performed)

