#### Patient accrual and study duration

We used an institutional database of patients with HNC and departmental treatment records to retrospectively approximate the number of patients that would have been eligible for this trial. Taking into account errors in electronic medical record documentation and coding [41, 42], we estimate that approximately 120–170 eligible patients were seen in our department over the past five years, roughly equating to two to three eligible patients monthly. These numbers are in line with or even slightly lower than what we have seen clinically recently, particularly as the COVID pandemic has subsided and more patients are being seen in our department. Additionally, our department’s recently closed phase II study of definitive HyperArc© SBRT in patients with recurrent, previously radiated HNC enrolled and treated the first fifteen patients in one year [15]. The patient population in this recently closed phase II trial is much narrower than that in the proposed study, so we anticipate similar if not faster enrollment with this proposed study compared with the recently closed phase II trial. As such, we anticipate enrollment of two to four patients monthly and that it will take approximately 15 months to complete the safety lead-in portion and 4 years to complete the study. Study-related data will be stored after completion of the clinical portion of the study to be used in the exploratory portion of the study, as needed.

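### The safety lead-in evaluation is fixed at the 15th enrollment, but its toxicity window runs to three months after PULSAR, and the trial calendar implies a later decision

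*Protocol article*

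**What the plan says.** Two places tie the evaluation to enrollment. Safety lead-in/interim analysis: "The study includes a safety lead-in portion, with formal evaluation on enrollment of the 15^th^ subject". Abstract, Methods: "A safety and feasibility evaluation will be performed after enrollment of the first fifteen patients".

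The stopping rule covers a longer period. Study design: "The first 15 enrolled patients will be evaluated in the safety lead-in portion", followed by the threshold, "If 5 or more of these 15 patients experience CTCAE v5.0 grade 3 or 4", or any grade 5 event. The toxicity counted is that "probably attributable to the intervention during or within three months after completion of PULSAR".

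Two other places give a time for the lead-in. Fig. 2 (Trial Calendar), footnote 8: "This will be the last follow-up for the safety lead-in portion, estimated to be at 12 months after trial opening". The footnote then describes what happens if the study goes on to its phase II portion. Patient accrual and study duration expects two to four enrollments a month and says "it will take approximately 15 months to complete the safety lead-in portion".

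**The concern.** An evaluation held when patient 15 enrolls cannot contain the data that the rule is defined on. That patient has had no fraction, and several earlier ones are still under treatment or within the three months after it. The calendar footnote points to a decision after follow-up, so the document gives two different times for one go/no-go decision.

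The Background says safety and feasibility must be validated before larger studies, and the lead-in is the only numerical safety stop in the article. If the enrollment wording were followed literally, a count below 5 could reflect missing follow-up rather than acceptable toxicity.

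**Working it through.** **Inputs from the article.** 15 lead-in patients; threshold 5. Treatment: "Patients will receive a total of 55 Gray in 5 fractions", one every 14 days (±10), so 4 × 14 = 56 days (1.84 months) from first to last fraction. Window closes 3 months after the last fraction. Accrual 2 to 4 per month.

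**Assumptions.** Lag from enrollment to first fraction 14 to 21 days (not stated); steady accrual; a true 40% rate of qualifying grade 3-4 toxicity; the any-grade-5 trigger left out.

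**Window length.** With a 14-day lag: 0.46 + 1.84 + 3 = 5.3 months from enrollment. With 21 days: 5.5 months.

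**Reproducing the calendar's 12 months.** The 15th enrollment falls (15 − 1)/rate months after the first.
- At 2 per month: 14/2 = 7.0 months. Adding 5.3 gives 12.3, which matches. Stopping at the last fraction gives 7.0 + 0.46 + 1.84 = 9.3, which does not.
- At 3 per month: 4.7 + 5.3 = 10.0. At 4 per month: 3.5 + 5.3 = 8.8.

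The 15 months in the accrual section needs a slower rate on the planned schedule: at 1.5 per month, 14/1.5 + 5.3 = 14.6. At 2 per month it is approached (14.1 to 14.6) only with a 28-day lag and the longest permitted intervals.

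**Data in hand at the 15th enrollment** (14-day lag, planned intervals). Patient i enrolled (15 − i)/rate months earlier.

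| Rate per month | Complete windows | Finished PULSAR | Share of window time observed |
|---|---|---|---|
| 2 | 4 of 15 | 10 of 15 | 58% |
| 3 | 0 of 15 | 8 of 15 | 40% |
| 4 | 0 of 15 | 5 of 15 | 28% |

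With a 21-day lag, 3 of 15 windows are complete at 2 per month. Over lags of 0 to 28 days and intervals of 4 to 24 days the count is 0 to 7 of 15, always a minority.

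**Chance of reaching 5 of 15.** With complete windows, P(X ≥ 5) for a binomial with n = 15 and p = 0.40 is 0.783. At the 15th enrollment, patient i contributes probability 0.40 × (fraction of the onset period already observed), and the tail is Poisson-binomial. Two onset patterns, each with a lag of 21 to 14 days:

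| Rate per month | Onset even over whole window | Onset even over the 56 treatment days only |
|---|---|---|
| 2 | 21-25% | 50-53% |
| 4 | about 1% | 19-27% |

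At a true 30% rate, even onset over the window and a 14-day lag, the figures are 48% with complete windows, 9.5% at 2 per month and 0.4% at 4 per month.

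**Enrollment during patient 15's window.** 2 × 5.3 = 10.6 to 4 × 5.5 = 22, so about 11 to 22 of the remaining 43 − 15 = 28 patients.

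**The case against.** The best reply is that the article already shows the intended timing. Footnote 8 speaks of a last lead-in follow-up and only then of proceeding, and its 12 months fits a wait for the three-month visit. That stands, and it limits the point: a reader might infer that the trial will in fact read its rule before most of the data exist, and the document does not establish this. Nor is it true of observed window time at 2 per month, where 52-64% has accrued for lags of 28 to 0 days. It is true of complete windows at every stated rate.

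The rule is also worded by event, and nothing closes the count at the evaluation. Toxicity is assessed within 7 days of each fraction, and the DSMB reviews each SAE monthly. These safeguards matter, so the probabilities above describe a single look and not the trial's whole protection. They do not replace the rule: no text asks the DSMB to keep the 5-of-15 count, and the AE severity section itself notes that a severe event need not be serious.

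Four further inferences are not supported:
- That three places give conflicting evaluation dates. The accrual section gives a duration, not an evaluation date.
- That the lack of a stated accrual hold is an error. A condensed article may leave this to the full protocol.
- That untreated patients dilute the count by a known amount. The article gives no number of untreated lead-in patients, and its drop-out allowance is not specific to them.
- That the triggers should be applied continuously. That would be a new stopping rule, not a reconciliation.

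**Conclusion.** The point holds as an internal contradiction with a real consequence if the wrong text is followed. The enrollment-based timing in the Abstract and in the lead-in section does not fit the rule's own window or footnote 8. With a 14 to 21 day lag and planned intervals, 0 to 4 of 15 windows are complete at the 15th enrollment. As a single look at an assumed 40% toxicity rate, the chance of triggering the count falls from 78% to about 21-53% at 2 per month and 1-27% at 4 per month.

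The direction does not depend on the onset pattern, since both patterns tried show a clear loss. The size does: later onset makes early reading worse and earlier onset makes it less harmful. The lag, the toxicity rate and the onset patterns are assumptions. The 12- and 15-month lead-in estimates also differ, which is a lesser matter because both are approximate.

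**What to change.** Reword the lead-in section and the Abstract to agree with footnote 8: the formal evaluation takes place once the lead-in patients have completed the three-month period after PULSAR, or have died or withdrawn earlier. Leave both stopping thresholds as they are. Give one estimate for the length of the lead-in in place of 12 and 15 months. State whether enrollment beyond patient 15 continues while the window runs.

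The cost is a wording amendment. The formal evaluation would come about 5 months later than the lead-in section now says. Accrual is delayed by that time only if it is held; if it is not held, about 11 to 22 more patients will have enrolled before the decision.
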